### 2.12. Primary outcome indicators

The primary outcome measure is the change in pain relative to baseline at the Western Ontario and McMaster Universities Osteoarthritis Index (WOMAC) from baseline to week 24. The most painful knee joint for the subject will be recorded at the baseline, which will be the joint we measured throughout the trial. We will also measure WOMAC pain at week 2, 8, 12, and 24.

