### 2.13. Secondary outcome indicators

The most important secondary outcome measurement is the improvement of WOMAC function. We will also assess the total score, function score, and stiffness score of WOMAC at baseline, week 2, 4, 8, 12, and 24. Visual analog scale pain score will be used to evaluate the arthritis pain of subjects at baseline, week 2, 4, 8, 12, 24. Short-form health survey 36 will be used to measure the quality of life of the subjects. In addition, we will evaluate the efficacy of a 5-point scale in the 4th week (1 = very poor, 2 = poor, 3 = general, 4 = OK, 5 = very good).

Any adverse event, whether related to treatment, requires the subject and investigator to report on each treatment or visit. Side effects included redness and blistering caused during treatment in both groups. Serious adverse events will be reported to the Ethics Committee. During the follow-up period (week 5–24), we will call the subject weekly to find out about the adverse reactions and side effects that may occur during the week.

After 4 weeks of treatment, the investigator will ask the subjects about the safety of the treatment including safe, fewer safe, safety problems, and serious safety problems. After each treatment, we will ask the subject’s feelings: “What do you feel during the treatment? 1. Heat; 2. Cold; 3. Pain; 4. no feeling; 5. Other, please describe.” The subjects will be allowed to take the analgesic or non-steroidal anti-inflammatory drugs used before the test, we will ask subjects to record the daily dose during the entire clinical trial, and then analyze the changes in the dose. We will measure the outcome of the baseline, week 2, 4, 8, and 12 at the investigation center. For the outcome of week 24, we will mail the questionnaire to the subjects and ask them to post them back after filling them out.

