### 2.17. Statistical analysis

The intent-to-treat analysis is the principle of this study and includes all subjects in a given treatment arm as well as subjects who complete at least 1 treatment course. The level of significant difference is set at 0.05. Baseline characteristics will be summarized for both groups of subjects. For continuous results, the normal distribution of the data is labeled as the mean (standard deviation). The primary outcome measure is the effect value of the WOMAC pain score from baseline, using the *t* test to compare the smoke-free moxibustion group with the traditional moxibustion group. For secondary outcomes, unpaired scores including WOMAC Pain, Function, and Stiffness Scores, Short-Form health survey 36, Expectedness and Reliability of Treatment, and Overall Treatment Outcomes will be compared at all follow-up time points in both groups. Continuous variables will be compared using *t* test or Wilcoxon rank-sum test. We will use SPSS version 22 (IBM SPSS Statistics, New York, NY) for statistical analysis.

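### The most important secondary outcome is improvement in WOMAC function, but the secondary analysis states no use of the baseline scores; each score should be adjusted for its own baseline

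*Protocol article*

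**What the plan says.** Section 2.13 ranks the secondary outcomes: "The most important secondary outcome measurement is the improvement of WOMAC function". It continues: "We will also assess the total score, function score, and stiffness score of WOMAC at baseline, week 2, 4, 8, 12, and 24". Table 1 confirms a pre-treatment value for WOMAC, VAS and SF-36.

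The secondary analysis in section 2.17 begins "For secondary outcomes, unpaired scores including WOMAC Pain, Function, and Stiffness Scores", adds SF-36, treatment expectation and credibility, and overall outcome to the list, and says that these "will be compared at all follow-up time points in both groups". On method it says: "Continuous variables will be compared using *t* test or Wilcoxon rank-sum test".

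For the primary outcome, section 2.12 says "The primary outcome measure is the change in pain relative to baseline", up to week 24. Section 2.17 keeps the reference to baseline there: "The primary outcome measure is the effect value of the WOMAC pain score from baseline, using the *t* test". The sentence on secondary outcomes has no such reference.

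**The concern.** An improvement is defined relative to a starting value. Section 2.13 names improvement in function as the leading secondary result, but section 2.17 lists only scores at each follow-up visit. It does not say that the baseline value enters the comparison, either by subtraction or as a covariate.

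In a trial of this size the arms will differ somewhat at baseline by chance, and an unadjusted comparison carries part of that difference into the estimate. The trial would measure baseline WOMAC, VAS and SF-36 and then forgo both the correction and the precision that these values offer.

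There is also a smaller matter. WOMAC pain is on the secondary list at all follow-up visits, and week 24 is one of them. The primary variable is therefore tested a second time, and nothing says how the two results relate.

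**Working it through.** **Inputs.** Section 2.16 gives 38 subjects per arm before the dropout allowance. The document gives no SD and no correlation between baseline and follow-up scores. I therefore work in units of the between-subject SD of a score at one visit, assume that SD equal at baseline and follow-up, and assume a correlation rho of 0.5, with 0.3 to 0.7 as the range. The plan states no figure on this point, so there is none to reproduce.

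**Step 1: size of chance imbalance.** The SE of the baseline difference between arms is sqrt(2/38) = 0.229 SD.

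**Step 2: what an imbalance d does to each analysis.**
- Follow-up score, unadjusted: the expected shift is rho × d.
- Change score, unadjusted: rho × d − d = −(1 − rho) × d, which is in the opposite direction.
- ANCOVA with baseline as covariate: no shift.

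For d equal to one SE (0.229 SD):

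| rho | Follow-up score | Change score | ANCOVA |
|---|---|---|---|
| 0.3 | 0.07 SD | −0.16 SD | 0 |
| 0.5 | 0.11 SD | −0.11 SD | 0 |
| 0.7 | 0.16 SD | −0.07 SD | 0 |

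**Step 3: precision.** The per-subject variances are 1 for the follow-up score, 2(1 − rho) for change and 1 − rho² for ANCOVA. The small cost of estimating the slope is ignored.

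| rho | Follow-up score | Change score | ANCOVA |
|---|---|---|---|
| 0.3 | 1.00 | 1.40 | 0.91 |
| 0.5 | 1.00 | 1.00 | 0.75 |
| 0.7 | 1.00 | 0.60 | 0.51 |

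ANCOVA has the smallest variance in every row. At rho 0.5, a variance of 0.75 from 38 per arm matches an unadjusted analysis with 38/0.75 = 50.7, or about 51 per arm.

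**Step 4: change or follow-up score as the response.** Write the follow-up score as Y, the baseline score as X and the arm as T. If Y = a + bT + cX, then Y − X = a + bT + (c − 1)X. The treatment effect b is the same in both. Once baseline is in the model, the choice of response does not matter, and b can be reported as the adjusted difference in improvement.

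**The case against.** **The text does not say that raw scores are compared.** This is right. 'Unpaired' most naturally describes a comparison of independent groups and leaves open whether each subject contributes a value or a change. A reader might infer that improvement is certainly never analysed, but that goes further than the text. Two features favour follow-up scores: the primary sentence refers to baseline and the secondary one does not, and the same wording covers the overall rating, for which Table 1 shows no pre-treatment value. That makes it the likelier reading, not a stated one. The case for adjustment does not depend on it, because Step 2 shows a shift on either reading.

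**Change scores would be enough.** They would not. Unadjusted change carries imbalance too, and at rho 0.3 it carries more than the follow-up score does and has the larger variance.

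**The two week-24 pain analyses could contradict each other on different scales.** A reader might infer this, but both are in WOMAC units and, under randomisation, estimate the same between-group difference. They differ through chance imbalance, precision and possibly the choice of test. Section 2.17 attaches no non-inferiority margin to the secondary tests, so a rate of conflicting non-inferiority verdicts would describe a procedure that the plan does not contain. If the secondary scores are changes, the week-24 t test is simply the primary test again. Sections 2.12 and 2.17 also make plain which outcome is primary.

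**This is detail for an analysis plan that is not shown.** That has force for the change-or-score wording and for the week-24 overlap, which are clarifications only. It has less force for the method: section 2.17 names the variables, visits and tests, and a better method is available from data already collected.

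**Conclusion.** The point holds as an improvement to the stated secondary analysis. It does not make that analysis invalid: over repeated randomisations, both unadjusted comparisons are unbiased. Section 2.13 promises improvement in function, and section 2.17 states no use of the baseline that improvement requires.

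With 38 per arm, a one-SE imbalance of 0.23 SD shifts either unadjusted comparison by about 0.11 SD at rho 0.5, and by 0.07 to 0.16 SD over rho 0.3 to 0.7. Adjustment removes that shift. At rho 0.5 it reduces the variance to about 0.75 of either alternative. These sizes rest on the assumed correlations, on equal SDs at the two visits and on a linear relation between baseline and follow-up. The document supplies none of these.

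The double listing of week-24 WOMAC pain is real but minor.

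**What to change.** In section 2.17, replace the t test or Wilcoxon comparison with ANCOVA for WOMAC function and for every other secondary score with a baseline value (WOMAC stiffness, total and pain, VAS and SF-36). Use that score's own baseline as the covariate. Report the WOMAC function result as the baseline-adjusted improvement that section 2.13 names. Outcomes with no baseline value, such as the 5-point rating, stay as planned.

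Add one sentence that either limits secondary WOMAC pain to visits other than week 24 or says that the primary analysis is decisive at that visit.

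The cost is a change of wording before the data are analysed. No further subjects, visits or measurements are needed, because Table 1 already collects the baseline values before treatment. Across the assumed range of rho, the adjusted analysis has a smaller variance than either unadjusted one.

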## 3. Discussion

The purpose of this study is to explore smokeless moxibustion as an effective moxibustion supplement and alternative therapy for the treatment of KOA. The trial will assess its non-inferiority compared to traditional moxibustion. Participants will receive 3 treatments per week. For external treatment of traditional Chinese medicine, the frequency of 3 times a week is the most commonly used method for the treatment of KOA. The use of single-blind randomized controlled trials in this trial can ensure the safety of subjects during the trial, and can also avoid the positive or negative effects of bias caused by subjective preferences for different therapies. This trial is a multicenter trial, which facilitates the collection of cases in a wide range in a short period of time, and the results are also more representative. This trial has some limitations. Due to the differences in the moxibustion materials used for smokeless moxibustion and traditional moxibustion, the operator will understand the grouping before placing the moxibustion box, which may lead to the operator’s basis. Therefore, operators will be rigorously trained in the assessment, treatment, follow-up, etc prior to the study. Traditional moxibustion produces strong smoke, which can be harmful to health,^[41]^ so many clinics and hospitals do not perform moxibustion therapy. New smoke-free moxibustion solves the problem of smoke produced by traditional moxibustion and also retains the warm effect, infrared characteristics, and unique odor of traditional moxibustion. Exploratory studies will help to determine the effect of new smokeless moxibustion and traditional moxibustion on serum parameters of KOA and explore objective parameters of clinical efficacy of KOA. This trial will provide reliable evidence for new smokeless moxibustion in the treatment of KOA and compensate for the lack of clinical efficacy research in this field.

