### 2.6. Randomization

A total of 88 subjects with KOA who are eligible per protocol will be randomly assigned to group A plant herbal activated carbon smokeless moxibustion group or group B traditional moxibustion group in a 1:1 ratio. After the investigator and the subject sign the informed consent, the investigator will perform a simple rheumatic examination. The investigator will make a diagnosis based on the knee X-ray film brought by the subject or the knee X-ray performed at the site. Only the subject who meet the inclusion/exclusion criteria will be randomized by a random number table. Then investigator will make a baseline assessment and arrange treatment.

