### 2.10. Treatment blinding

Both smokeless moxibustion and traditional moxibustion are placed in an unmarked moxibustion box after ignition. Their appearance and operation procedures are the same. The combustion of moxa sticks in the box is invisible. The masked description used in the consent is as described in the “method/design and setting” above so that the subjects will be blinded until the completion of the study. The whole process is supervised by the coordinator of our study team in each center. All subjects in the study will be treated by trained operators. Due to the difference in the amount of smoke burned by the 2 kinds of moxa sticks, subjects of 2 groups will be treated in separate treatment rooms to avoid communication.

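### Operators admitted to know the allocation are answered only with training that covers assessment and follow-up, leaving the subjective centre-visit outcomes and the baseline of the primary change score open to influence

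*Protocol article*

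**What the plan says.** Section 3 (Discussion) states as a limitation that "the operator will understand the grouping before placing the moxibustion box" and that this may bias the operator. The next sentence gives the response: "Therefore, operators will be rigorously trained in the assessment, treatment, follow-up, etc prior to the study".

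Section 2.10 describes blinding of subjects: unmarked boxes, identical appearance and procedure, and separate rooms. The rooms are separate "Due to the difference in the amount of smoke burned by the 2 kinds of moxa sticks". It adds supervision: "The whole process is supervised by the coordinator of our study team in each center". Neither this section nor any other describes a masked outcome assessor.

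On collection, section 2.13 says "We will measure the outcome of the baseline, week 2, 4, 8, and 12 at the investigation center". For week 24 the method differs: "we will mail the questionnaire to the subjects and ask them to post them back after filling them out". Section 2.12 defines the primary outcome as the change in WOMAC pain "from baseline to week 24. The most painful knee joint for the subject will be recorded at the baseline". Section 2.6 describes eligibility checks and randomisation, and continues: "Then investigator will make a baseline assessment and arrange treatment".

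**The concern.** The remedy does not answer the limitation it is offered for. The stated problem is knowledge of the arm, and a trained operator still has that knowledge. By including assessment and follow-up in the training, the sentence also suggests that the people just named as a source of bias may take part in collecting outcomes.

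Most centre-visit outcomes are reports by the subject that can be coloured by whoever asks the question or is in the room: WOMAC (including function, which section 2.13 ranks as the leading secondary outcome), VAS, the week-4 five-point rating and the week-4 safety question. The weekly safety calls in weeks 5 to 24 are similar.

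The primary outcome is reached by a narrower route. It is a change score, so its baseline value counts as much as its week-24 value. If baseline WOMAC pain and the choice of index knee are recorded after allocation by someone who knows the arm, both are open to influence. In a non-inferiority trial of a new product, a preference for that product pushes towards the claim.

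**Working it through.** **1. Who knows the arm, and what masks them.** Operators know it (section 3). Subjects are blinded by the box and separate rooms (section 2.10). Supervision by a coordinator or study staff (sections 2.7 and 2.10) is oversight, not masking. For operators, the only measure named is training.

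**2. Which outcomes are exposed, by time point.**

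| Time point | How collected | Exposure |
|---|---|---|
| Baseline | At the centre, by the investigator, placed after randomisation (2.6, 2.13) | Enters the primary change score; index knee also fixed here (2.11, 2.12) |
| Weeks 2, 4, 8, 12 | At the centre; who completes the form is not stated (2.13) | WOMAC and VAS at each; five-point rating and safety question at week 4 |
| Weeks 5 to 24 | Weekly telephone calls; caller not named (2.13) | Reported adverse reactions |
| Week 24 | Posted questionnaire completed by the subject (2.13) | Operator not involved in collection |

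Serum markers (2.14) and the timed 50-yard walk (abstract) are not subjective reports, so this argument does not extend to them in the same way.

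**3. The baseline route.** Primary change = week-24 score minus baseline score. Section 2.17 compares the groups by t test. A shift of b points in the baseline of one arm only therefore moves the group difference in change by b. Section 2.3 needs a baseline VAS of at least 40 for eligibility, so a VAS reading must exist before randomisation. WOMAC is not an eligibility criterion, so nothing in section 2.3 brings its baseline forward. The Table 1 column for the period before treatment fits either order.

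**4. Illustration of size (assumed, not taken from the documents).** Inputs from section 2.16: margin 0.10 × 184.87 = 18.487, which reproduces the stated 18.49; alpha 0.025, taken as one-sided; power 80%; 38 per group. The article prints no SD. Solving the normal-approximation formula with a true difference of 0:

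SD = 18.49 × √(38/2) / (1.960 + 0.842) ≈ 28.8

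(An SD of 28.4 gives 38 per group in the sample-size function used here, so the implied SD is about 28.4 to 28.8.)

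SE = 28.77 × √(2/38) = 6.60

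If the new arm is truly worse by exactly the margin and a shift b favours it, the type I error is 1 − Φ(1.960 − b/SE):

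| Shift b (WOMAC points) | b/SE | One-sided type I error |
|---|---|---|
| 0 | 0 | 0.025 |
| 2 | 0.30 | 0.049 |
| 5 | 0.76 | 0.115 |

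In SD units, b/SE = d × √(38/2) = 4.36d, so the SD cancels. For d = 0.1, b/SE = 0.436 and the error is about 0.06. For d = 0.2, b/SE = 0.872 and the error is about 0.14.

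These figures show sensitivity only. They assume that the whole shift reaches the primary change score, which here could happen at the assessment stage only through baseline.

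**The case against.** The strongest reply is that the primary follow-up score is already protected in the way recommended here: subjects complete it at home and post it back. Subject blinding, unmarked boxes and supervision are also stated. That stands. A reader might infer from section 3 that training is the trial's only safeguard; it is only the remedy given there for operator bias.

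Second, the text does not say that operators score any form. A reader might infer it from the training sentence, but section 2.6 gives the baseline assessment to the investigator, section 2.13 has the investigator ask the safety question, and the other centre-visit collectors are not named. A condensed article may leave such detail to the full protocol. That stands as to who holds the pen. It does not rescue the sentence in section 3, which expressly answers an admitted bias with training in assessment. Nor does the article say that the investigator is unaware of the arm when taking baseline; since that person then arranges treatment, and the arms use separate rooms, awareness is plausible but inferred.

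Third, the move from centre to post between baseline and week 24 applies to both arms alike. It may add noise, but no bias between arms follows from it alone.

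Fourth, self-completion does not deal with an operator who influences a subject over 12 sessions, or with a subject who infers the arm from the smoke. That also stands.

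**Conclusion.** The point holds in a limited form. Section 3 states a bias risk and gives a remedy that cannot mask the people concerned, while no masked assessor is described for the centre visits. The outcomes mainly affected are the subjective ones at weeks 2 to 12, plus the baseline value and index-knee choice behind the primary change score if these follow the order in section 2.6.

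The size is not known. The type I error figures rest on an assumed shift and on 38 analysed per group; the versions in WOMAC points also rest on an SD inferred from the sample size. It is tempting to express the bias as a share of the 18.49 margin and conclude that the primary result is at risk by that amount. The documents do not support this: no observer effect is given, the week-24 score is collected without the operator, and the exposed secondary scores have no stated margin. The amendment is worth making because it is cheap and closes a stated weakness, not because the primary conclusion has been shown to be unsafe.

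**What to change.** 1. In sections 2.10 and 2.11, and in place of the training sentence in section 3, state that operators who treat a subject do not administer, and are not present for, that subject's outcome assessments or weekly safety calls.
2. Have subjects complete WOMAC, VAS, SF-36, the five-point rating and the safety question themselves wherever these are scheduled, on the same form that is posted at week 24.
3. Amend section 2.6 so that the baseline questionnaire and the index-knee choice are recorded before allocation is known. Steps 1 and 2 alone would leave the present order in place.
4. Keep the operator limitation in section 3, worded to say that these steps reduce operator influence and do not remove it.

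The cost is some reassignment of tasks and scheduling at each of the three centres. Whether existing staff suffice cannot be judged from the article, since staffing is not described. The week-24 questionnaire is already planned, and the sample size, margin and treatment do not change.
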